#### 2.8.2. Data and Safety Monitoring

Interim safety reports are performed by the sponsor to the independent data monitoring and safety committee (DMSC), consisting of two clinician-scientists and a methodologist-biostatistician, each time 40 patients are enrolled [14], including blinded variables on randomization-stratification variables (site, severe ARDS, COVID-19, and shock at enrollment), serious and unexpected adverse events, and the rates and causes of death at day 28. An interim analysis is preplanned on data from 350 patients (175 by group), with symmetric group sequential flexible stopping boundaries [41]. Recommendations for continuing, pausing, or stopping the study will be made by the DMSC to the steering committee for superiority of either active or control, or potential safety reasons. The observation of differences in serious adverse events between the two groups allows unblinding of the group allocations if deemed necessary by the DMSC.

#### 2.8.3. Statistical Considerations

The statistical analysis plan is provided in Supplementary Material File S7. A two-sided *p* value < 0.05 will be considered for significance of all analyses, except for interim analysis. The primary analysis will be performed using an intention-to-treat (ITT) principle. Then, we will perform per-protocol and subgroup analyses on the primary and secondary outcomes (Table 3). The primary endpoint (VFD28) will be analyzed using a mixture of generalized gamma distributions to concatenate the overall frequency and distribution of the times [42]. Multivariable adjustments will be performed in (1) a first model including only the randomization-stratification variables and center as random-effect; (2) a second model with covariates from the first model and covariates with clinically relevant relationships with the outcome and significant in univariate analyses (*p* < 0.10). The key secondary outcome of day 90 survival will be evaluated using the Kaplan–Meier approach and compared using the log-rank test (univariate analysis); multivariable adjustments will be conducted using the same two models described above. Because of the potential for type I error due to multiple comparisons, findings for analyses of other secondary endpoints will be interpreted as exploratory.

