### 2.4. Randomization

All patients were randomized online (CSOnline, Clinsight) by local investigators within 24 h of meeting inclusion criteria on a 1:1 ratio for the two study arms. The randomization sequence was generated by minimization and stratified by the study center, the degree of ARDS severity (PaO_2_/FiO_2_ < 100 mmHg), the suspicion or presence of COVID-19, and the presence of shock (defined as intravenous infusion of vasoactive drugs) at enrollment.

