#### 2.8.4. Sample-Size Justification

Total enrollment will target 700 patients (350 by group). The trial is designed with >80% power to detect a difference of 2 days alive and off ventilation at day 28 (primary outcome of VFD28), with standard deviation of 8 [43,44] and two-sided type I error of 5%. For this calculation, we assumed the variability of VFD28 would follow the properties of ROSE [21], the Esophageal Pressure-guided Ventilation-2 (EPVent-2) trial [45], and a pilot study of inhaled sevoflurane in ARDS [14], with 28 day mortality around 30–35% [21,24,45].

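### As worded, the final VFD28 test keeps p < 0.05 after a superiority look at half the sample, which does not fit an overall two-sided 5% error; the excess is small unless the boundary is Pocock-type

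*Protocol article*

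**What the plan says.** Three statements in the protocol article bear on the type I error of the primary comparison.

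- Section 2.8.2 (Data and Safety Monitoring): "An interim analysis is preplanned on data from 350 patients (175 by group), with symmetric group sequential flexible stopping boundaries". The same section lets the monitoring committee recommend stopping because either the active or the control arm is superior, as well as for safety.
- Section 2.8.3 (Statistical Considerations): a two-sided p value below "0.05 will be considered for significance of all analyses, except for interim analysis".
- Section 2.8.4 (Sample-Size Justification): "Total enrollment will target 700 patients (350 by group"), with ">80% power to detect a difference of 2 days alive and off ventilation at day 28", "with standard deviation of 8" and a "two-sided type I error of 5" per cent.

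Section 2.8.2 cites a source for the boundaries. The article gives no interim nominal level, spending function, interim endpoint or reduced final level. Section 2.8.3 places the statistical analysis plan in Supplementary File S7, which is not at hand.

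**The concern.** A group sequential design holds its overall error only if the interim and final critical values come from the same boundary. Error used at the interim has to be taken from the final test. Section 2.8.3 adjusts one of the two looks and leaves the other at the full level. If the interim boundary can be crossed at all, the chance of a false claim at one look or the other is then above 5%.

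In practice this concerns a final VFD28 p value that lies between the level the boundary leaves and 0.05. The sentence in section 2.8.3 would call it significant and the sequential design would not. The Discussion says that a gain in VFD28 should prompt wider use of inhaled sedation, so the threshold should be beyond dispute before the final data are seen.

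**Working it through.** **Inputs from the article.** 350 patients per group, difference 2 days, SD 8, two-sided 5% (section 2.8.4); allocation "on a 1:1 ratio for the two study arms" (section 2.4); interim at 350 of 700, an information fraction of 0.5 (section 2.8.2); final threshold 0.05 (section 2.8.3).

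**Assumptions, because the article is silent.** The interim tests VFD28 with the same statistic as the final analysis, and the boundary is one of five common forms.

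**Step 1: the plan's own figure.** The expected final z is 2 / (8 × √(2/350)) = 3.307. Power at two-sided 0.05 is Φ(3.307 − 1.960) = Φ(1.347) = 91.1%. This agrees with the stated power of more than 80%, for which 252 per group would be enough. The section 2.8.4 calculation is therefore sound, and it has room to spare.

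**Step 2: overall error with the final test left at 0.05.** Under the null, the interim and final z values are bivariate normal with correlation √0.5 = 0.707. For an interim critical value c₁,

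overall error = 1 − P(|Z₁| < c₁ and |Z₂| < 1.960).

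**Step 3: the final level that restores 5%.** Solve 1 − P(|Z₁| < c₁ and |Z₂| < c₂) = 0.05 for c₂. Then recompute power with mean 3.307 × 0.707 = 2.339 at the interim and 3.307 at the end.

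| Assumed interim boundary | Interim p | c₁ | Overall error, final at 0.05 | c₂ for 5% overall | Final nominal p | Power after correction |
|---|---|---|---|---|---|---|
| Haybittle-Peto | 0.001 | 3.291 | 5.02% | 1.962 | 0.0498 | 91.1% |
| O'Brien-Fleming-type spending | 0.00305 | 2.963 | 5.10% | 1.969 | 0.0490 | 91.0% |
| Classic O'Brien-Fleming | 0.0052 | 2.794 | 5.20% | 1.978 | 0.0480 | 90.9% |
| Pocock | 0.0294 | 2.178 | 6.74% | 2.178 | 0.0294 | 88.3% |
| Pocock-type spending | 0.0310 | 2.157 | 6.86% | 2.201 | 0.0277 | 88.0% |

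The excess over 5% is 0.02 to 0.20 percentage points in the first three rows and 1.74 to 1.86 points in the last two. With O'Brien-Fleming-type spending, only a final p between 0.0490 and 0.05 would be misclassified. With Pocock-type spending the band runs from 0.0277 to 0.05.

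**The case against.** The strongest reply is that the article does commit to group sequential boundaries. Such a set normally includes the final critical value, and its details belong in File S7. On this view the 0.05 sentence is a general convention that also covers secondary, per-protocol and subgroup analyses, and the 5% in section 2.8.4 is the overall level.

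Part of this stands. The shape of the boundary and the exact final level may properly be left to the analysis plan, and their absence from the article is no fault. But section 2.8.3 does more than stay silent. It states a p-value cut-off for every analysis and exempts the interim alone. If File S7 sets a lower final level, the article contradicts it; if File S7 repeats 0.05, the error is not held. The sentence needs correcting in either case.

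A reader might infer something stronger: that the trial's type I error is in fact inflated, by as much as 6.9%. The documents do not support that. File S7 may already set the final level. The article does not say that the interim tests VFD28, and with another endpoint the figures above would not apply as given. Nothing in the article points to a Pocock-type boundary, so 6.9% is the result of one assumed example and not a bound derived from the plan.

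It is also fair to object that with a conservative boundary the excess is too small to change how most results would be read. That stands, and it limits the weight of the point.

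**Conclusion.** The inconsistency is in the text. A superiority look at 350 of 700, a final test at the full 0.05 and an overall two-sided error of 5% cannot all hold. How much it matters depends on a boundary that the article does not name. If the interim tests VFD28, the overall error would be about 5.02% to 5.2% with a Haybittle-Peto or O'Brien-Fleming-type boundary, which is slight, and 6.7% to 6.9% with a Pocock-type boundary, which is material. The point is therefore moderate: a threshold to be reworded and reconciled, and a serious fault only if the boundary proves to be Pocock-type. The sample size and the stated power are not in question.

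**What to change.** Reword the sentence in section 2.8.3 to say that 0.05 is the overall two-sided level for the primary outcome across the interim and final analyses, and that the final VFD28 test uses the nominal level left by the chosen boundary. That level would be, for example, 0.0490 with O'Brien-Fleming-type spending or 0.0277 with Pocock-type spending at an information fraction of 0.5. Name the boundary and the interim endpoint, check the wording against File S7 so that both documents give the same final level, and settle this before the final data are seen. The confidence interval reported with the primary result should match that level.

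The cost is a sentence or two and some power. On the stated inputs, power goes from 91.1% to about 91.0% with O'Brien-Fleming-type spending, or to 88.0% with Pocock-type spending, a loss of about three points. Both remain above the stated 80%, and no extra patients are needed.

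### Model 2 picks its extra covariates partly by univariate p < 0.10 on the trial's own outcomes, so its covariate set is not fixed in advance

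*Protocol article*

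**What the plan says.** All of this stands in section 2.8.3 of the protocol article, unless noted.

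- The first adjusted model is fully specified in its terms: "a first model including only the randomization-stratification variables and center as random-effect".
- The second keeps the terms of the first and adds "covariates with clinically relevant relationships with the outcome and significant in univariate analyses", the threshold for the univariate analyses being p < 0.10.
- For the key secondary outcome, 90-day survival, "multivariable adjustments will be conducted using the same two models described above". The rule therefore serves both VFD28 and survival.
- The significance level is common to them: "A two-sided *p* value < 0.05 will be considered for significance of all analyses", with the interim analysis excepted.
- Further detail is placed elsewhere: "The statistical analysis plan is provided in Supplementary Material File S7". That file is not shown.
- Section 2.8.4 gives the size: "Total enrollment will target 700 patients (350 by group").

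**The concern.** In a randomized comparison, adjustment is there to gain precision and to correct chance imbalance. Both aims are served by covariates already known to be prognostic, and these can be named before any outcome is seen. A p-value screen replaces that knowledge with a noisy test on the same outcome that the model will analyse. Strong predictors pass almost always, so the screen adds little for them. Weak ones enter or leave largely by chance.

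Two consequences follow. The model 2 result comes from a model that nobody could write down beforehand. And because the screen refers to the outcome being modelled, VFD28 and 90-day survival may end up adjusted for different variables, which makes the two adjusted results harder to read together.

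This is a rule that the article states, not a detail that it leaves to the analysis plan. File S7 may list the candidates. Even then, under the published rule, the trial's own p-values would decide which of them stay.

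**Working it through.** **The plan's own figure first.** Inputs from section 2.8.4: 350 per group, difference 2 days, SD 8, two-sided 5%. The standard error is 8 × √(2/350) = 0.605. The ratio is 2/0.605 = 3.307, and power is Φ(3.307 − 1.960) = Φ(1.347) = 0.911. The stated power of more than 80% is met. The point does not rest on this figure, and the sample size does not change.

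**How stable is the selected set?** Take a covariate whose true correlation with the outcome is r, tested at two-sided p < 0.10 (critical value 1.645) in N = 700. On the Fisher z scale the standard error is 1/√(N − 3), so, treating r as its own transform for small r and ignoring the negligible opposite tail,

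P(enters) ≈ 1 − Φ(1.645 − r√697), with √697 = 26.40.

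| r (assumed) | r√697 | 1.645 − r√697 | P(enters) | Two identical trials disagree, 2P(1 − P) |
|---|---|---|---|---|
| 0.05 | 1.320 | 0.325 | 37% | 2 × 0.37 × 0.63 = 47% |
| 0.10 | 2.640 | −0.995 | 84% | 2 × 0.84 × 0.16 = 27% |

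For weak predictors, then, the covariate set is largely a matter of chance. The formula is for a continuous outcome. For the planned mixture model and for survival it is an approximation.

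**Does the instability damage type I error?** This was simulated with 700 patients, 1:1 allocation, no treatment effect, a normal outcome, least squares, and 3,000 runs per setting. There were 5 to 15 candidate covariates, each explaining 2 to 4% of outcome variance. These numbers and strengths are assumptions; the article gives none.

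| Candidates, variance share each | Unadjusted | All candidates, fixed list | Every covariate passing p < 0.10 | Better of unadjusted and screened | Best result found among passing covariates, effect visible |
|---|---|---|---|---|---|
| 5, 2% | 4.6% | 4.4% | 4.4% | 6.0% | 8.3% |
| 10, 2% | 4.9% | 4.9% | 4.9% | 7.1% | 15.7% |
| 10, 4% | 5.9% | 6.2% | 6.2% | 9.3% | 27.5% |
| 15, 2% | 5.2% | 5.1% | 5.2% | 8.1% | 28.0% |

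Monte Carlo error is √(0.05 × 0.95/3000) = 0.4 points. In every row the mechanical screen behaves like the fixed list. The 6.2% in the third row appears in both columns, with 5.9% unadjusted in the same runs, so it cannot be charged to screening.

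A separate simulation (1,500 replicates, eight candidates with r from 0.05 to 0.30) agrees: 5.7% when every screened covariate is entered, with Monte Carlo error √(0.05 × 0.95/1500) = 0.56 points, and 12.9% when the most favourable subset is kept.

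The first three result columns describe rules that never look at the treatment effect. The last two describe a choice made with the effect in view. Only those two depart from the nominal level.

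**The case against.** The strongest defence has four parts.

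*The screen does no demonstrated harm to error rates.* This stands. The case for changing the rule is pre-specification and stability, not type I error.

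*Steering is not in the text.* A reader might infer that the relevance judgement is made after the fact on trial data, so that analysts could keep whichever covariates favour sevoflurane, with error rates of 13% or even 28%. The article does not support that. Only the univariate screen is tied to trial data. Clinical relevance may be settled beforehand from prior knowledge, and neither entry condition mentions the treatment effect. Who judges relevance, when, and from which candidates are matters that an article commonly leaves to the analysis plan. The high figures need a search for the best result with the effect visible, under assumed inputs and a linear model rather than the planned generalized gamma mixture.

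*Model 2 is only the second adjusted analysis.* This also stands. Model 1 has fixed terms, the log-rank comparison of survival is labelled univariate, and nothing in the article makes model 2 the confirmatory result. A reader might infer that the primary conclusion is compromised; the text does not show that.

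*Different endpoints may have different prognostic factors, and the article speaks of the same two models.* This is fair: differing sets are possible, not certain. Likewise, the dependence of hazard-type effects on the covariate set applies to any adjusted model, including a fixed one, and is no separate argument against screening.

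What the defence does not remove is the stated rule itself. No candidate list in File S7 would make the final set known in advance while p < 0.10 decides who stays.

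**Conclusion.** The point holds as one about pre-specification. The covariate set of model 2 depends on the trial's own outcome p-values, for VFD28 and for 90-day survival. A covariate correlating 0.05 with the outcome enters about 37% of the time and one correlating 0.10 about 84%, under the stated approximation at N = 700. Mechanical screening leaves type I error at about 5%. Inflation would arise only if relevance were judged, or a model chosen, with treatment results visible, and the article neither says nor rules out that this happens. Model 1 and the sample size are untouched. The change is worth making because it is cheap and removes the question, not because an error in the trial's conclusion has been shown.

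**What to change.** Before unblinding:

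1. Delete the p < 0.10 condition from model 2.
2. Name a short list of baseline prognostic covariates to be added to the model 1 terms. Age and baseline SOFA are examples. PaO2/FiO2 is another, with one caution: section 2.3 and Table 1 allow enrolment on SpO2/FiO2 when no blood gas is available, so the protocol's own imputation (Table 1 notes, referring to File S1) should be used for those patients.
3. Use the same list for VFD28 and 90-day survival, whatever the univariate p-values.

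The cost is a change of wording; no patients need be added. The small downsides are that a few weak covariates may be carried, each taking one parameter in a model fitted to 700 patients, and that some baseline values may need imputation. If File S7 already holds a candidate list, the change reduces to using that list without the screen.

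### Allocation is minimized on four factors, but 90-day survival is compared with a univariate log-rank, and no result is named as confirmatory for either VFD28 or 90-day survival

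*Protocol article*

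**What the plan says.** Section 2.4 states that the sequence was "generated by minimization and stratified by the study center", together with ARDS severity (PaO2/FiO2 below 100 mmHg), suspected or present COVID-19, and shock.

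Section 2.8.3 then sets out the analyses:

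- **VFD28.** "The primary endpoint (VFD28) will be analyzed using a mixture of generalized gamma distributions". Two multivariable adjustments follow. Model 1 is "a first model including only the randomization-stratification variables and center as random-effect". Model 2 keeps those terms and adds "covariates with clinically relevant relationships with the outcome and significant in univariate analyses", with a threshold of p < 0.10.
- **90-day survival.** Kaplan–Meier curves are "compared using the log-rank test (univariate analysis"), and then "multivariable adjustments will be conducted using the same two models described above".
- **Significance.** One two-sided 0.05 threshold applies to every analysis except the interim. The multiplicity caveat covers only the other secondary endpoints.

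The Discussion says that wider use of inhaled sedation should be considered if either VFD28 or 90-day survival is improved.

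**The concern.** Minimization makes the arms more alike on its factors than chance would. If those factors predict outcome, the treatment estimate varies less than an unadjusted test assumes. The test then rejects a true null less often than 5%, and it has less power than an analysis that includes the factors. The article itself treats low PaO2/FiO2 as a marker of worse prognosis and points to large differences in ARDS management between centres, so some prognostic strength is plausible.

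The second issue is rank. Each of the two leading endpoints carries a lead analysis, model 1 and model 2, all read at 0.05. The content of model 2 depends on outcome associations found in the trial. Since a benefit on either endpoint is meant to support a change of practice, the article should leave no doubt about which result counts.

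**Working it through.** **1. The plan's own figure.** Inputs from section 2.8.4: 350 per arm, difference 2 days, SD 8, two-sided 5%.

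- SE = 8 × √(2/350) = 0.605; 2/0.605 = 3.307.
- Power = Φ(3.307 − 1.96) = 91.1%.

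This agrees with the stated power of more than 80%; 252 per arm would give 80% and 337 per arm 90%.

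**2. VFD28 with and without the factors.** Let the balanced factors explain a share R² of outcome variance (an assumption; the article gives no value), and let s = √(1 − R²). A normal approximation stands in for the gamma mixture, because the article's own sample-size calculation uses a mean difference and an SD.

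- Unadjusted true size = 2 × [1 − Φ(1.96/s)]
- Unadjusted power = Φ((3.307 − 1.96)/s)
- Adjusted power = Φ(3.307/s − 1.96)

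| R² | unadjusted size | unadjusted power | adjusted power |
|---|---|---|---|
| 0.05 | 4.4% | 91.7% | 92.4% |
| 0.10 | 3.9% | 92.2% | 93.7% |
| 0.20 | 2.8% | 93.4% | 95.9% |

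For R² = 0.10: s = 0.949, 1.96/s = 2.066 and size = 3.9%. Unadjusted power is Φ(1.420) = 92.2% and adjusted power is Φ(1.526) = 93.7%.

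The gap widens for a smaller true effect. At 1 day, power is 37.7% unadjusted and 39.6% adjusted for R² = 0.05, and 36.6% and 45.6% for R² = 0.20.

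**3. 90-day survival.** Simulation of 700 patients in 37 centres with three binary factors. The following are assumptions: minimization assigning the balancing arm with probability 0.8, 42% baseline 90-day mortality, hazard ratio 0.75, factor prevalences of 45%, 50% and 60%, and three levels of prognostic strength. There were 2,500 runs per scenario. The plain log-rank is compared with one stratified on the three binary factors.

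| Factors | size, plain | size, stratified | power, plain | power, stratified |
|---|---|---|---|---|
| Weak | 5.0% | 5.0% | 64.4% | 64.7% |
| Moderate | 4.0% | 4.6% | 62.2% | 64.4% |
| Strong | 3.5% | 4.4% | 57.9% | 62.4% |

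Monte Carlo error on a size near 5% is √(0.05 × 0.95/2500) = 0.4 points. The direction is clear for moderate and strong factors, and nothing of note is lost with weak ones.

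**4. Three results at 0.05.** A null simulation of VFD28 used the same minimization, SD 8 and a linear model, with factors explaining 7% or 10% of variance (assumed; 2,500 trials). At least one of the unadjusted, model 1 and model 2 results fell below 0.05 in 7.0% or 6.9% of trials, with Monte Carlo error of about 0.5 points. This is a rough indication, because it depends on the assumed covariates. Screening at p < 0.10 leaves the type I error of model 2 alone near 5%, so the risk comes from the choice among results and not from the screen by itself.

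**The case against.** The strongest reply is that the remedy is mostly in the plan already. Model 1 is prespecified for both endpoints, and the article refers to an analysis plan (File S7, not shown) that may say which result leads. A conservative test also does not raise false positives. Both points stand, and they limit the weight of the concern. They do not remove it: the univariate log-rank is a stated choice of method, and so is one 0.05 threshold for all analyses. Neither is a detail left to another document.

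A reader might go further than the text allows in three ways.

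- **That the primary VFD28 test is unadjusted.** The article never says so. Only the log-rank is labelled univariate; for VFD28 it is an inference from the adjustments being listed afterwards.
- **That the deciding p-values are conservative.** No result is named as deciding, so the documents cannot show that the deciding one is unadjusted.
- **That the trial falls short of its planned power.** With the article's inputs, power is 91.1% before any adjustment, and step 2 keeps it above that figure for the 2-day effect.

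Model 2 also requires clinical relevance, so the p < 0.10 screen is not its only filter.

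**Conclusion.** The point holds in a limited form. The key secondary comparison is stated as univariate after minimized allocation, model 1 is placed as a later adjustment for both endpoints, and no result is named as confirmatory. The statistical cost is modest: a true size of 4.4% to 2.8% for an unadjusted VFD28 test, a gain of about 1 to 2.5 power points at the 2-day design effect, and about 0 to 4.5 points for the log-rank. These sizes rest on assumed R², prognostic strengths, event rate and hazard ratio, none of which the article gives. If the factors are weakly prognostic, almost nothing is lost in power, and the remaining gain is that the confirmatory result is fixed in advance. The change is worth making; it is not a flaw that threatens the trial.

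**What to change.** In section 2.8.3 and the analysis plan:

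- Name model 1 as the primary analysis of VFD28.
- For 90-day survival, make the confirmatory test a log-rank stratified on severity, COVID-19 and shock, or a Cox model with those terms and a centre random effect. Name one of the two.
- Report the unadjusted results and model 2 as sensitivity analyses.
- Replace the p < 0.10 screen in model 2 with a list of baseline covariates fixed before unblinding.

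The cost is wording only. The factors are already recorded at randomization, and neither the sample size nor the data collection changes.
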